### Safety assessment

3.4

ASF has a long history in Chinese traditional medicine and is widely used in hospitals. The experimental dose is within the recommended range, which is based on the People's Republic of China Pharmacopeia (2015 edition). The vital signs (blood pressure, pulse, body temperature, respiration) of patients will be measured regularly. Physical examinations will be carried out, and blood biochemistry will be monitored regularly. Adverse reactions of the 2 groups will be monitored by the modified COMBINE SAFTEE, a structured instrument for collecting adverse events adapted for clinical studies in the alcoholism field.

### Compliance

3.5

During the treatment phase, the researchers will record the type, frequency, and dose of any drug received by the patient during the hospitalization, monitor the patient's medication compliance ((drug bags distributed-returned bags)/total number of prescription bags) and other medications taken during the treatment period, and copy any relevant clinical records made at the time of admission. Another researcher who does not participate in the training management and is blinded to the treatment allocation of the patients will contact follow-up interviews including abstinence and TLFB, during the follow-up period after treatment. According to the intention-to-treat principles, patients who withdraw from treatment will still be contacted by researchers for follow-up before completing the 6 weeks of treatment, unless they withdraw from the study.

### Adverse events

3.6

All the adverse events that occur during the trial will be examined and documented in this study. The adverse events, which refer to any unintended and undesirable signs (such as abnormal laboratory test results), diseases or symptoms that occur after treatment in the process of clinical trial, do not necessarily have causal relationships with this treatment. The adverse events will be recorded through observation or patient complaints. The incidence of adverse events between the 2 groups will be examined according to occurrence frequency. Once any serious adverse event occurs, the intervention should be stopped immediately. According to China Food and Drug Administration (CFDA) Standard Operating Procedures (SOPs), the intervention time, relationship with the drug, severity, and actions taken will be recorded in detail. In addition, serious adverse events should be reported to the Ethics committee within 24 hours.

### Data management and quality control

3.7

All the records in the CRFs are filled out and collected by trained and qualified researchers. After the CRF is completed, the original data recorded won’t be changed, even if any changes are made. The clinical examiner will review all the completed CRFs. A medical statistician will guide data entry and management. In order to ensure the accuracy of the data, 2 data managers will input and proofread the data independently. Once the established database is reviewed, it will be locked by key researchers and statistical analysts. The locked files or data will not be changed and will be submitted to the statistics team for statistics and analysis. The scientific research department of the Affiliated Hospital of Chengdu University of traditional Chinese medicine will review the data in the middle of the study.

### Statistical analysis

3.8

Data analysis will be performed using the SPSS 18.0 statistical software package. Categorical variables will be compared by use of chi-square analysis. Continuous variables between groups will be analyzed by independent sample *T* test. The repeated measure of analysis of variance (ANOVA) will be used to analyze the differences in the group. For all reported values will be expressed as mean ± SEM. The log-rank test will be applied to compare the cumulative probability functions. The Cox proportional hazards model will be applied to assess the hazard ratio of achieving 12 weeks of abstinence and the Kaplan–Meier method will be used to calculate the cumulative probability function of reaching 12 weeks of abstinence. The changes of desire measured by PACS will be compared at baseline and at week 6 through the *T* test. The changes of desire and resistance during the study will be analyzed by using mixed linear regression analysis. All statistical tests will be two-sided tests, and *P* < .05 indicates that the difference is statistically significant.

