### Sample size

2.4

This study adopts a randomized, controlled, double-blind clinical trial design. Based on data from the study by Johnson et al,^[18]^ where withdrawal rate was 54.5% in the treatment group and16.7% in the control group, with an alpha of 5%, and a power of 90%, the estimated sample size for the 2 groups was 68 patients using the PASS 15 software (34 patients in each group). With an estimated dropout rate of 20%, a total number of 82 patients (41 patients in each arm) will be needed.

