### Outcome measures

3.2

Primary outcomes: The primary outcomes are the changes in the average daily alcohol consumption of the 2 groups before and after treatment and comparison of the scores of the psychological craving self-rating scale during the courses of treatment of 2 groups.

Secondary outcomes: The secondary outcomes include abstinence rates of the 2 groups during the follow-up period, days without consumption, and changes of Short Form Health Survey (SF-36) scores in 2 groups before and after therapy.

The researchers will use weekly self-reports during the follow-up period, clinicians’ judgments, and biochemical examinations to determine whether the patient is abstinent. If the patient has drunk no more than 1 cup since the last visit, the GGT level is normal, or has not increased since the last examination, and the respiratory alcohol concentration is less than 0.10 g/L, the patient is judged to abstain from alcohol.

From the first week to the sixth week, vital signs will be monitored daily. The physical examination will be carried out weekly. The respiratory alcohol concentration will be measured once a week, and drinking craving and adverse events will be evaluated weekly at the time of enrollment and at weeks 2, 4, 6, and 7, serum γ-glutamyl transpeptidase (γ-GT) and blood alcohol concentration will be detected. At weeks 0, 3, and 6, the doctors will give the patients electrocardiograms, and urine pregnancy, blood routine and blood biochemical levels will be detected. During the follow-up period, serum γ-GT and respiratory alcohol concentration will be measured once a week.

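### The unadjusted t test on change in alcohol consumption is inefficient if the sizing rates mean no drinking; a baseline-adjusted, rank-based test would recover most of the lost power

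*Protocol article*

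**What the plan says.** Section 3.2 (Outcome measures) names two primary outcomes. The one at issue is "the changes in the average daily alcohol consumption of the 2 groups before and after treatment".

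Section 3.8 (Statistical analysis) gives a general rule: "Continuous variables between groups will be analyzed by independent sample" t test. The other methods listed there serve other purposes. Repeated-measures ANOVA is for differences within a group, mixed linear regression is for desire and resistance, and log-rank and Cox are for time to abstinence. So the t test is the only between-group method that fits consumption. No baseline covariate, transformation or rank method is mentioned for it. "All statistical tests will be two-sided tests", at 5%.

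Section 2.4 (Sample size) uses a cited study "where withdrawal rate was 54.5% in the treatment group and16.7% in the control group", with 90% power, and reports that "the estimated sample size for the 2 groups was 68 patients using the PASS 15 software (34 patients in each group"). It then adds: "With an estimated dropout rate of 20%, a total number of 82 patients (41 patients in each arm) will be needed". Withdrawal rate is not defined, and no mean, SD or distribution of consumption is given anywhere.

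**The concern.** The 54.5% v 16.7% could well be abstinence rates. The larger figure belongs to the treated arm, it is the effect to be detected, and dropout is handled separately at 20%. On that reading, about half the ASF arm and a sixth of the placebo arm would report no drinking after treatment, and the rest would form a right-skewed tail.

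A t test on raw change handles such data poorly for two reasons. The change score carries all the between-patient variation in baseline intake. What remains is driven by the heaviest drinkers, not by the patients who move to zero. The trial could then miss, on a primary outcome, an effect as large as the one it was sized on.

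**Working it through.** **1. The plan's own figure.** Inputs from section 2.4: p1 = 0.545, p2 = 0.167, two-sided 5%, 90% power. Mean rate 0.356, difference 0.378.

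n = [1.960 × √(2 × 0.356 × 0.644) + 1.282 × √(0.545 × 0.455 + 0.167 × 0.833)]² / 0.378²
= [1.960 × 0.677 + 1.282 × 0.622]² / 0.1429 = 4.514 / 0.1429 = 31.6, so 32 per arm.

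With continuity correction it is 37. The stated 34 lies between the two. Exact power at 34 per arm is 92.9% (pooled z) or 88.4% (Fisher). The 82 follows from 34 × 1.2 = 40.8, so 41 per arm.

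**2. The same effect seen by the consumption tests: one case by hand.** Assumptions, none from the documents: baseline mean 1 with CV 0.7; drinkers' mean m = 0.5 of baseline with CV 0.8; lognormal, log-scale correlation 0.5; drinkers alike in both arms; zeros in 54.5% v 16.7%.

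- Mean difference = 0.378 × 0.5 = 0.189.
- Post-treatment variance = (1 − p) × m² × (1 + 0.8²) − [(1 − p) × m]². ASF: 0.1866 − 0.0518 = 0.135. Placebo: 0.3415 − 0.1735 = 0.168.
- Covariance with baseline = (1 − p) × m × [exp(0.5 × 0.631 × 0.703) − 1], where 0.631 = √ln(1.49), 0.703 = √ln(1.64) and the bracket is 0.249. ASF 0.057, placebo 0.104.
- Variance of change = 0.49 + post variance − 2 × covariance. ASF 0.512, placebo 0.451.
- **t test on change:** SE = √[(0.512 + 0.451) / 34] = 0.168; 0.189 / 0.168 = 1.12; power ≈ Φ(1.12 − 1.96) = 20%.
- **ANCOVA on grams:** residual variance = 0.1514 − 0.0801² / 0.49 = 0.138 (0.1514 and 0.0801 are the averages over arms); SE = √(2 × 0.138 / 34) = 0.090; 0.189 / 0.090 = 2.10; power ≈ Φ(2.10 − 1.96) = 55-56%.

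The baseline variance of 0.49 is about three times the post-treatment variance of about 0.15. Most of the t test's loss in this case therefore comes from using an unadjusted change score.

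**3. Simulation over ranges (power, %).**

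| Scenario | t on change | ANCOVA on grams | Rank ANCOVA |
|---|---|---|---|
| The case in step 2, 34 per arm | 19-22 | 57-59 | 81-83 |
| Same, 41 per arm | 24-25 | 63-65 | 87-88 |
| CV 0.5-1.0, drinkers at 30-80% of baseline, correlation 0.6, 34 per arm | 8-58 | 48-78 | 81-84 |
| As the row above, ASF drinkers also drink 30% less | – | 83-99 | 95-99 |
| Zeros 40% v 15%, 33 per arm | 8-18 | 20-34 | 46 |
| Zeros 30% v 10%, 33 per arm | 7-13 | 14-24 | 33 |
| Zeros 10% in both arms, ASF drinkers drink 40% less, 33 per arm | – | 45-81 | 48-80 |

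(33 per arm is 82 × 0.8 = 65.6, halved. A dash means that no figure is reported here.)

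At CV 1.0 ANCOVA has 47-51% against 81-82% for rank ANCOVA; at CV 0.5 the gap is 5-7 points. Replacing exact zeros by 0-2 g/day, to mimic the one-cup allowance in the abstinence definition, moved power by at most 4 points.

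**4. Type I error.** With equal zeros in both arms (16.7% or 35.6%), rejection was 4.2-4.6% for the t test, 4.5-4.6% for ANCOVA and 4.7-5.2% for rank ANCOVA.

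**The case against.** **The rates may not be zero-drinking rates.** A reader might infer that the plan's own figures imply a large, unequal spike at zero. They do not. Withdrawal rate is undefined. Abstinence is a secondary outcome, assessed in follow-up, and it allows up to one cup. Week-6 consumption covers the past month, so a zero needs a whole month without a drink. This stands: the power figures are conditional on that reading.

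**Baseline adjustment may be enough.** A reader might also infer that the zero spike defeats the analysis even after adjustment. The figures do not support that. ANCOVA roughly triples power in the central case and finds the effect more often than not unless spread is high. This stands too.

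**Equal intake among drinkers favours ranks.** The protocol expects ASF to reduce craving, so continuing drinkers may also cut down. The gap between ANCOVA and rank ANCOVA then narrows to little or nothing except at high spread. The t test gains as well: at 33 per arm, CV 0.5 and drinkers at 80% of baseline, it reaches 87% if ASF drinkers drink 30% less. That is its favourable corner; with 40% less drinking at CV 0.7 and drinkers at 50% of baseline it is still only 45%.

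**A rank test answers a different question.** The primary is a change in an average, and the rank P value does not refer to a mean difference. This is a real cost, and the two summaries could disagree. Nor is rank ANCOVA the only candidate: a two-part test had 87% in the central case.

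**An article condenses.** Distribution checks may sit in an unseen analysis plan. But the article does not merely stay silent; it states a test, and that test is the weak one.

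**Conclusion.** The point holds as a conditional loss of efficiency. If the sizing rates are rates of no drinking after treatment, the stated t test on raw change has about 8-58% power at 34 per arm, against about 93% for the two-proportion comparison that sized the trial. ANCOVA on grams raises this to about 48-78% and rank ANCOVA to about 81-84%.

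These figures rest on assumed spreads, residual drinking and correlation, and on drinkers being alike in the two arms. Smaller differences in zeros lower every figure. Within the scenarios run, rank ANCOVA was never materially worse than ANCOVA and was far better than the t test. The case against the unadjusted change score is strong; the case for ranks over ANCOVA is moderate and depends on spread. The test is valid, so no false-positive risk arises. The change is worth making, with medium confidence in the size of the gain.

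**What to change.** In section 3.8, before unblinding, replace the unadjusted t test on change in consumption with a baseline-adjusted analysis. Name as the prespecified test a rank ANCOVA: ranked week-6 average daily consumption on arm and ranked baseline consumption. Report the baseline-adjusted difference in mean daily consumption with a bootstrap 95% CI as the effect size.

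Because the P value will refer to a shift in distribution, state that the rank test decides and that the mean difference is descriptive. Defining withdrawal rate in section 2.4 would show whether the condition above applies.

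The cost is wording in section 3.8 and the analysis plan. Baseline consumption is already collected at week 0, no patients are added, and SPSS can run it, with one extra step for the bootstrap. The same test could be considered for days without consumption, which is bounded and may pile up at its maximum; no calculation was made for that secondary outcome.

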### Questionnaires

3.3

At week 0 and week 6, as well as during the follow-up period, the examiner will work closely with the patient to fill in this Timeline Follow Back (TLFB) schedule for the past month, based on the alcohol diary collected weekly. The TLFB has been widely evaluated and tested,^[19]^ and in previous studies,^[20]^ it has been proved to have high retest reliability. The data collected by TLFB will be applied to evaluate the effects on the primary outcomes and secondary outcomes.

Baseline data for the Clinical trial, the Alcohol Use Disorders Identification Test (AUDIT) questionnaire, the TLFB interview, and the diagnostic instruments or questionnaires for diagnosis of alcohol addiction will be collected routinely for all patients. At week 0 and week 6, as well as during the follow-up period, the questionnaires will be conducted including: demographics (age, gender, marital status, occupation), alcohol consumption (TLFB), withdrawal symptoms (CIWA-Ar), alcohol addiction (MAST), craving (Pennsylvania Alcohol Craving Scale (PACS)), drinking behaviors (AUDIT), health status (SF-36), psychopathology (Symptom Checklist (SCL-92)),drug use (DUDIT), and adverse events (COMBINE Systematic Assessment For Treatment Emergent Events (COMBINE SAFTEE)).

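### The t tests fixed for the two primary outcomes do not adjust for baseline, and craving has two analyses with neither named as primary

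*Protocol article*

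**What the plan says.** Section 3.2 (Outcome measures) names two primary outcomes. One is a before-and-after change in intake: "The primary outcomes are the changes in the average daily alcohol consumption of the 2 groups before and after treatment". The other compares the arms on a craving self-rating scale over the course of treatment.

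Section 3.8 (Statistical analysis) then fixes the methods:

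- The general rule is "Continuous variables between groups will be analyzed by independent sample" t test.
- Repeated-measures ANOVA "will be used to analyze the differences in the group", which reads as a within-arm analysis.
- For craving, "The changes of desire measured by PACS will be compared at baseline and at week 6" by a t test.
- Directly after that, "The changes of desire and resistance during the study will be analyzed by using mixed linear regression analysis".
- All tests are two-sided at P < .05. No covariate is named, and no analysis is labelled primary.

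On timing, Section 3.2 says "drinking craving and adverse events will be evaluated weekly". Section 3.3 (Questionnaires) places PACS in a battery introduced by "At week 0 and week 6, as well as during the follow-up period, the questionnaires will be conducted including".

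**The concern.** Baseline intake (TLFB at week 0) and baseline PACS are both collected, and both are likely to predict the week-6 value. A change score uses baseline only by subtraction, with a fixed coefficient of 1. ANCOVA estimates that coefficient and is at least as precise in large samples. In a trial planned on 68 evaluable patients, an avoidable loss of precision matters.

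The craving outcome has a second problem. A week-6 t test and a longitudinal regression answer somewhat different questions and could disagree. Without a named primary analysis, either could be put forward as the result on a primary outcome. The regression sentence states no arm contrast, and its term resistance is not tied to any scale listed in Section 3.3.

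Finally, if PACS is completed only at the times listed in Section 3.3, the regression would have no PACS values between week 0 and week 6.

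**Working it through.** **Which test serves which outcome.** Consumption is defined as a change (Section 3.2) and falls under the general t-test rule, so the planned comparison is a change-score t test. No other between-arm method in Section 3.8 fits it. The PACS sentence does not say whether its t test is paired or between arms. Because Section 3.2 frames craving as a comparison of the two groups, I read it as a between-arm test of change.

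**Inputs.** The article gives no figure to reproduce here. Its sample size (Section 2.4) rests on two proportions and supplies no SD, effect size or correlation for either primary outcome. Assumptions: equal SDs at baseline and end of treatment (set to 1), correlation r from 0.3 to 0.8, and, for power only, a true difference of 0.5 SD. From Section 2.4: 34 per arm before the dropout allowance.

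**Formulas.** Relative variance of the arm difference:

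- change-score t test: 2(1 − r)
- ANCOVA: 1 − r²
- ratio, change to ANCOVA: 2(1 − r) / [(1 − r)(1 + r)] = 2/(1 + r)

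Power = Φ(0.5 / (σ√(2/34)) − 1.96), where σ is the square root of the relative variance. The equivalent size is 68 × ratio: the number of patients a change-score test needs to match ANCOVA on 68.

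| r | Change | ANCOVA | Ratio | Equivalent of 68 | Power, change | Power, ANCOVA |
|---|---|---|---|---|---|---|
| 0.3 | 1.40 | 0.91 | 1.54 | 105 | 41% | 58% |
| 0.5 | 1.00 | 0.75 | 1.33 | 91 | 54% | 66% |
| 0.7 | 0.60 | 0.51 | 1.18 | 80 | 76% | 82% |
| 0.8 | 0.40 | 0.36 | 1.11 | 76 | 90% | 93% |

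**If the SDs differ.** With end-of-treatment SD equal to s times baseline SD, the change-score variance is 1 + s² − 2rs and the ANCOVA variance is s²(1 − r²). The difference is (1 − rs)², which is never negative, so the direction does not depend on equal SDs. The size does. At s = 0.5 the variances are 1.25 − r and 0.25(1 − r²). At r = 0.5 these are 0.75 and 0.1875, a ratio of 4. This is an illustration; nothing in the article fixes s.

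**Two craving analyses.** If success on either were accepted at 5%, two independent tests would give 1 − 0.95² = 9.75% type I error. These two share data and would normally be positively correlated, so the figure would lie between 5% and 9.75%. The article does not say that success on either would suffice.

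**Timing.** Section 3.2 names drinking craving weekly but no instrument. Section 3.3 names PACS but lists week 0, week 6 and follow-up. If the weekly measure is PACS, the mixed model has repeated treatment-period values. If not, week 6 is the only PACS value after baseline within treatment, and an average over treatment cannot be estimated.

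**The case against.** The strongest reply is that nothing invalid is planned. A change-score t test is unbiased under randomisation, a mixed model for craving is already in the plan, and covariates are commonly left to a fuller document. The precision figures rest wholly on assumed correlations and shrink to 11% at r = 0.8. They also describe the t tests, not the mixed regression, so they bear mainly on consumption. On timing, Section 3.3 does not say PACS is given only at the listed times. The weeks 2, 4, 6 and 7 that follow the weekly-craving phrase in Section 3.2 most naturally belong to the γ-GT and blood alcohol measurements. The SPIRIT schedule (Figure 1), which is not available here, may settle the matter.

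Most of this stands, and it limits the point to precision and clarity. It does not remove it. The article does not leave the between-arm method open; it states a t test. Nor does the mixed-regression sentence say which craving analysis decides the primary outcome.

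A reader might infer four stronger things that the article does not support:

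- **That baseline values are thrown away.** They enter both change scores by subtraction.
- **That weekly craving scores are thrown away.** The mixed regression covers desire during the study.
- **That regression to the mean biases the comparison.** In expectation it acts equally on both randomised arms.
- **That within-arm ANOVA is planned as evidence of efficacy.** Its wording is loose, but Section 3.8 provides a between-group test and nothing says a within-arm fall will count for ASF.

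**Conclusion.** The point holds as one of efficiency and specification. For consumption, the only stated between-arm test omits baseline adjustment. With equal SDs, that costs 11% to 54% in variance over r = 0.8 to 0.3; at r = 0.5, 68 patients under ANCOVA are worth about 91 under change scores. The correlation, the equal SDs and the 0.5 SD effect behind the power figures are assumptions. That ANCOVA is at least as precise in large samples does not depend on them.

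For craving, two analyses stand side by side with neither named primary and no arm contrast stated. Whether the weekly craving measure is PACS cannot be settled from Sections 3.2 and 3.3. The planned tests remain valid, so this should be improved before analysis; it does not undermine the trial.

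**What to change.** **Consumption.** Replace the t test with ANCOVA of end-of-treatment mean daily intake on arm and baseline intake. Baseline TLFB is already collected.

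**Craving.** Make the planned mixed model the single primary analysis. Include baseline PACS as a covariate and state one arm contrast in advance: the difference at week 6, or the difference averaged over treatment. Keep the week-6 t test as supportive, and say which scale the term resistance refers to.

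**Schedule.** Reconcile Sections 3.2 and 3.3 so that both say whether the weekly craving measure is PACS.

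**Cost.** If the weekly measure is PACS, these are changes of wording with no new data. If it is not, adding PACS weekly is a small extra questionnaire burden. Without it, the contrast should be the week-6 difference.

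### Two primary outcomes are each judged at two-sided P < .05 with no rule linking them to the efficacy claim, so the error rate can reach 9.75% if either one suffices

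*Protocol article*

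**What the plan says.** Section 3.2 (Outcome measures) gives two primary outcomes on an equal footing, as does the abstract. The first: "The primary outcomes are the changes in the average daily alcohol consumption of the 2 groups before and after treatment". The second: "comparison of the scores of the psychological craving self-rating scale during the courses of treatment of 2 groups". The same section has craving assessed weekly during treatment.

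Section 3.8 (Statistical analysis) sets one decision rule for the whole trial: "All statistical tests will be two-sided tests, and *P* < .05 indicates that the difference is statistically significant".

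Three sentences in section 3.8 bear on how the primary outcomes are tested:

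- A general rule for continuous variables: "Continuous variables between groups will be analyzed by independent sample *T* test".
- A rule for craving at two time points: "The changes of desire measured by PACS will be compared at baseline and at week 6 through the *T* test".
- A rule for craving over time: "The changes of desire and resistance during the study will be analyzed by using mixed linear regression analysis".

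The article does not say which craving analysis is the primary one, or how the results on the two outcomes combine into a conclusion about ASF.

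**The concern.** With two primary outcomes, the phrase 'the trial is positive' needs a definition. As written, a P value below .05 on consumption alone, on craving alone, or on both would each count as a significant primary result. A reader of the eventual report could not tell whether a win on one and a loss on the other was meant to count as success. If it was, the chance of at least one false significant primary result is higher than the 5% attached to each test.

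Craving has a second opening. The week-6 t test and the mixed regression can give different answers, and nothing fixed in advance says which one speaks for the outcome. If these choices are left until the data are unblinded, they can be made to suit the results.

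**Working it through.** **Inputs.** Two primary outcomes (section 3.2). Each is tested two-sided at 0.05 (section 3.8). The correlation between the two test statistics is not given, so a range from 0 to 0.9 is assumed. The article states no familywise figure to reproduce; it states only the per-test 5%.

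**Step 1: either outcome suffices, independent tests.**
Familywise error = 1 − (1 − 0.05)² = 1 − 0.9025 = 0.0975, or 9.75%.

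**Step 2: either outcome suffices, correlated tests.** Treat the two statistics as bivariate normal under no effect on either outcome, with critical value 1.96. The familywise error is 1 − P(|Z₁| < 1.96 and |Z₂| < 1.96).

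**Step 3: direction.** The tests are two-sided, so each has a 2.5% chance of a false result favouring ASF. For independent tests, the chance that at least one does so is 1 − 0.975² = 0.0494. With correlation, it is 1 − P(Z₁ < 1.96 and Z₂ < 1.96).

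| Assumed correlation | Either significant, two-sided | Either significant in favour of ASF |
|---|---|---|
| 0 | 9.75% | 4.9% |
| 0.3 | 9.5% | 4.8% |
| 0.5 | 9.1% | 4.5% |
| 0.7 | 8.3% | 4.2% |
| 0.9 | 7.0% | 3.5% |

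For one test, the matching values are 5% and 2.5%. The ratio to a single test is 9.75/5 = 1.95 at correlation 0 and 7.0/5 = 1.4 at correlation 0.9.

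**Step 4: both must succeed.** The familywise error is then not inflated, since a false claim needs two significant results. The article does not state this rule.

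**Step 5: after a correction.** Testing each outcome at 0.025 gives 1 − 0.975² = 4.94% if independent and 4.65% at correlation 0.5, so at most 5%. Holm starts from the same 0.025 and has the same error when neither outcome has an effect.

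**Step 6: which craving analysis.** Section 3.2 defines the outcome over the course of treatment. The t test uses only baseline and week 6. Its wording can be read as comparing the two groups' changes, or as comparing the two time points within a group; on the second reading it does not test a treatment effect at all. The mixed regression uses the repeated scores and is closer to the outcome definition. However, its period is the whole study, which could also take in the 12-week follow-up.

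**The case against.** The strongest objection is that this is a condensed article. Success rules and multiplicity procedures are often placed in an analysis plan, which is not shown here. The article states 5% per test and never claims 5% for the trial as a whole, so it does not contradict itself. This limits the point but does not remove it. The article does more than stay silent: it prints a threshold for all tests, and any later multiplicity procedure would have to override that sentence.

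The introduction calls this a pilot protocol. It also gives verifying efficacy as an aim, and an efficacy claim needs a success rule.

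A reader might infer more than the document supports, in four ways:

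- **Three or more competing craving tests.** The repeated-measures ANOVA is worded as within-group and does not mention craving, and the week-6 t test may also be within-group. Within-group tests are not extra chances at a treatment effect. No count of competing tests, and no larger error rate built on one, can be taken from the text.
- **The alpha in section 2.4 is breached.** The sample size was worked "with an alpha of 5" per cent for a single comparison of withdrawal rates (54.5% against 16.7%), which is neither primary outcome.
- **A known loss of power if both outcomes must succeed.** The 90% power in section 2.4 belongs to that same comparison. The article gives no power for consumption or craving, so no joint power can be derived.
- **A near 10% chance of falsely declaring ASF effective.** The 9.75% counts false results in both directions.

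The objection on correlation also stands. The introduction treats craving as the driver of renewed drinking, so a positive correlation is plausible and 9.75% is the top of the range.

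**Conclusion.** The point holds in a limited form. Two co-equal primary outcomes are each judged at two-sided .05, and no rule connects them to the conclusion on efficacy. If either outcome suffices, the two-sided familywise error runs from about 7.0% (correlation 0.9) to 9.75% (independent), and the share favouring ASF from about 3.5% to 4.9%. 'Nearly double' is fair only at low to moderate correlation.

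The figures rest on three assumptions: that either outcome suffices, that there is one between-group test per outcome, and that the statistics are bivariate normal. The open choice of craving analysis is a further weakness that the text does not allow one to quantify. This should be fixed. It does not invalidate the design.

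**What to change.** Before unblinding, amend section 3.8 as follows:

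1. Replace the flat threshold, for the two primary outcomes only, with one stated procedure. Either use Holm or Hochberg across the two at an overall two-sided 5%, or use a fixed sequence in which the second outcome is formally tested only if the first is significant at 5%. The order is for the sponsor to set; the article gives none.
2. Name one between-group analysis for each primary outcome. For consumption, the independent-samples t test on change already fits the general rule. For craving, the mixed regression best matches the outcome definition; state the between-group contrast and confine it to the treatment period.
3. Say whether the week-6 t test is between or within groups, and label it and all other tests supportive.

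The cost is one paragraph, with no new data or visits. Under a fixed sequence, the second outcome is tested conditionally. Under Holm, the smaller P value must be below 0.025 before the other is tested at 0.05. Either way, a little power is lost on one outcome.
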